## Abstract

**Background:**

As the first meal of the day, breakfast plays an important role in supplying energy and nutrients, which are critical to working and learning activities. A three-phase crossover study was designed to investigate the effects of breakfast on cognitive function among Chinese white-collar workers. The planned study protocol is presented.

**Methods:**

A total of 264 participants aged 25–45 years will be recruited from Shenyang and Chongqing. Self-administered questionnaires will be used to collect information on age, gender, marital status, education level, occupation, smoking habits, drinking habits, and breakfast behaviours. The participants will be randomly assigned to 3 equal-sized groups (Groups A, B, and C) and will be provided with a nutrition-adequate breakfast, a nutrition-inadequate breakfast, or no breakfast, respectively. Each participant will receive the breakfast treatment on the basis of assignment to one of three sequences (ABC/BCA/CAB). Each participant will complete a battery of cognitive tests assessing short-term memory, attention, and working memory 120 minutes after breakfast. Mood will be measured through a self-administered questionnaire assessing the dimensions of positive and negative frames of mind. Additionally, fasting blood glucose and postprandial 2-hour blood glucose levels will be tested with a blood-glucose meter (Roche ACCU-CHEK®-Performa). All the participants will take all the tests in three successive weeks, and the order of presentation will be counter-balanced across groups.

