### Sample size calculation and participants

In a related study, the average cognitive performance value of people who ate a nutrition-adequate breakfast, a nutrition-inadequate breakfast and no breakfast has been found to be 36.6, 25.9 and 26.8, respectively [20]. Using these results as reference values, in this study, power is set at 0.8, SAS programming was used, and the necessary sample size was calculated. According to the SAS procedures described by Hu [21], we calculated the sample size as 117 in one city. If the dropout rate is 10%, a total of 130 participants will be needed. Given that the participants will be divided into three groups, and to achieve equal group sizes, 44 participants will be needed for each group. Therefore, 132 participants will be needed for the three groups to include an equal number of men and women in one city. Because this study will be conducted in two cities, 264 total participants will be recruited.

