### Participants and study design

Participants will be recruited from two cities, Shenyang and Chongqing, China. Shenyang is located in northeast China, whereas Chongqing is located in southwest China.

The inclusion criteria will be: white-collar workers aged 25–45 years involved mainly in office work, who engage in brain work and are amenable to skipping breakfast.

The exclusion criteria will be: individuals with mental illness, oral disease or other severe diseases; pregnant women and nursing mothers; individuals who have a tendency to lose weight; and individuals who never eat breakfast.

This crossover study will last for three weeks. Participants will be randomly assigned to one of three groups (Group A, Group B, and Group C). In the first week, Group A will be provided with a nutrition-adequate breakfast, Group B will be provided with a nutrition-inadequate breakfast, and Group C will be provided with no breakfast. Each participant will complete tests of blood glucose level, mood, hunger and satiety, and cognitive function. In the second week, Group A will be provided with no breakfast, Group B will be provided with a nutrition-adequate breakfast, and Group C will be provided with a nutrition-inadequate breakfast. Each participant will complete blood glucose level, mood, hunger and satiety, and cognitive function tests. In the third week, Group A will be provided with a nutrition-inadequate breakfast, Group B will be provided with no breakfast, and Group C will be provided with a nutrition-adequate breakfast. The blood glucose level, mood, hunger and satiety, and cognitive function will be tested again. All participants will take the tests in three successive weeks, and each participant will be tested in three breakfast treatments: nutrition-adequate breakfast, nutrition-inadequate breakfast, or no breakfast. The study design is presented in Fig. 1.

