### Study procedure

Each participant from each of the three groups will receive the designated breakfast and complete the tests for three successive weeks, and the order of presentation will be counter-balanced across the groups. All participants will be instructed to fast from 20:00 pm the night before the study. The next morning, the participants will arrive at the designed location at 07:30 am. All the participants will rest in a seated position for 10 minutes and provide a finger-prick blood sample for the blood glucose test (blood glucose meter, Roche ACCU-CHEK®-Performa). Subsequently, participants from the groups that consume a nutrition-adequate and a nutrition-inadequate breakfast will have 15 minutes to ingest their breakfast in the designed location under the supervision of investigators until the breakfast is completely eaten. The breakfast will be delivered by the investigators. During this interval, the participants in the no breakfast treatment group will rest for 15 minutes. After 120 minutes, a second finger-prick blood sample from each participant for the blood glucose test will be collected. Then, all the participants will complete a series of tests on mood, sense of hunger and satiety, and cognitive function. All the tests will be performed under similar laboratory conditions (quiet room, 22–24 °C). Testing will not occur on Mondays, because the diets of the participants over the weekend is likely to be more varied than usual and, in the case of poorly nourished participants, lower in energy intake. The study procedure is shown in Fig. 2.

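### One cyclic set of three orders balances breakfasts over weeks but not over the preceding breakfast; all six orders would cost almost nothing more

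*Protocol article*

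**What the plan says.** The Methods part of the Abstract allocates participants "on the basis of assignment to one of three sequences (ABC/BCA/CAB") and states that "the order of presentation will be counter-balanced across groups". Study procedure repeats that "the order of presentation will be counter-balanced across the groups".

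Participants and study design gives the schedule week by week:

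- Week 1: "In the first week, Group A will be provided with a nutrition-adequate breakfast, Group B will be provided with a nutrition-inadequate breakfast"; Group C gets nothing.
- Week 2: "In the second week, Group A will be provided with no breakfast, Group B will be provided with a nutrition-adequate breakfast"; Group C gets the inadequate one.
- Week 3: "In the third week, Group A will be provided with a nutrition-inadequate breakfast, Group B will be provided with no breakfast"; Group C gets the adequate one.

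Write A for adequate, B for inadequate and C for none. The schedule is then ACB, BAC, CBA. The Abstract's strings, read as orders of meals, run round the cycle the other way.

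On spacing, the same section says "All participants will take the tests in three successive weeks". On numbers, Sample size calculation and participants says that "to achieve equal group sizes, 44 participants will be needed for each group", which is per city. Analysis strategy plans a repeated-measures ANOVA with breakfast within subjects and sex between subjects.

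**The concern.** In a crossover, the order set decides what can be separated from the treatment effect. A 3×3 cyclic square removes week effects. It leaves each treatment with one fixed predecessor, so a residual effect of the previous week's treatment always lands on the same successor.

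The tests are repeated weekly, and the attention test reuses the same letters. The Study hypothesis is that an adequate breakfast improves performance. If people also learn a task better in their adequate-breakfast week, part of that gain could show the following week. Under the week-by-week schedule that is always the no-breakfast week; under the Abstract's orders it is always the inadequate-breakfast week. Both are comparators in the Study hypothesis. With one cyclic set, a check that adjusts for such an effect is also costly in precision.

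**Working it through.** **1. The plan's own numbers.** From Sample size calculation and participants: 117 / 0.90 = 130 per city; 130 / 3 = 43.3, raised to 44 per group; 3 × 44 = 132 per city; 2 × 132 = 264. These reproduce and are not in dispute.

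**2. Predecessors.** There are six possible ordered pairs (previous breakfast → current breakfast).

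| Order set | Pairs that occur | Times each |
|---|---|---|
| Week-by-week schedule: ACB, BAC, CBA | A→C, C→B, B→A | 2 |
| Abstract: ABC, BCA, CAB | A→B, B→C, C→A | 2 |
| All six orders | all six | 2 |

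**3. Bias without a carry-over term.** Let L_A, L_B and L_C be the amounts carried into the next week. In a three-order set each breakfast has a predecessor in two of its three appearances.

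- Week-by-week schedule: the mean carry-over received is (2/3)L_B for A, (2/3)L_C for B and (2/3)L_A for C. The bias is therefore (2/3)(L_B − L_A) in A−C, (2/3)(L_B − L_C) in A−B and (2/3)(L_C − L_A) in B−C.
- Abstract's orders: A receives (2/3)L_C, B receives (2/3)L_A and C receives (2/3)L_B. The bias in A−B is (2/3)(L_C − L_A).
- All six orders: each breakfast follows each of the others in 2 of 6 appearances. The bias in A−C is (1/3)(L_C − L_A) and in A−B is (1/3)(L_B − L_A).

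Now set L_A = 1 and the others to 0:

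| Order set | A−C | A−B | B−C |
|---|---|---|---|
| Week-by-week schedule | −2/3 | 0 | −2/3 |
| Abstract | 0 | −2/3 | +2/3 |
| All six | −1/3 | −1/3 | 0 |

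**4. What cancels.** If L_A = L_B = L_C, every expression in step 3 is zero. A common practice gain also cancels. With an assumed 0, 3 and 5 points in weeks 1 to 3, each breakfast gets (0 + 3 + 5)/3 on average, so every contrast shifts by 0.

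This needs equal sequence sizes or a week term. Suppose completers were 44, 40 and 34 (assumed) in ACB, BAC and CBA, with no week term. The mean gain is then 290/118 for A, 332/118 for C and 322/118 for B. The shifts are −0.36 in A−C, −0.27 in A−B and −0.08 in B−C. A week term returns all three to 0.

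**5. Cost of adjusting for carry-over.** Take the model with participant, week, breakfast and first-order carry-over.

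- Unadjusted variance of a pairwise contrast: 2σ²/N in every design, where σ² is the within-participant variance.
- For a carry-over contrast with coefficients scaled to Σc² = 1, the within-participant sum of squares is c₁² + c₂² − (c₁ + c₂)²/3, where the subscripts number the weeks. Because c₁ + c₂ = −c₃, its average over orders is 1/3 + 1/3 − 1/9 = 5/9.
- The overlap coefficient from step 3 is 2/3 for three orders and 1/3 for six. Efficiency after adjustment is 1 − (overlap²)/(5/9).
- Three orders: 1 − (4/9)/(5/9) = 1/5. Six orders: 1 − (1/9)/(5/9) = 4/5.

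A numerical least-squares check on the design matrices gives the same ratios:

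| | Three orders | Six orders |
|---|---|---|
| Unadjusted variance, N = 264 | 2/264 = 0.00758σ² | 0.00758σ² |
| Adjusted variance, N = 264 | 10/264 = 0.03788σ² | 2.5/264 = 0.00947σ² |
| Inflation | 5 | 1.25 |
| Adjusted standard error | 0.19σ | 0.10σ |

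**6. Scale.** The protocol's reference means differ by 36.6 − 26.8 = 9.8 (adequate versus none) and 36.6 − 25.9 = 10.7 (adequate versus inadequate). An assumed 1.5 points carried over from the adequate week alone would shift adequate versus none by −(2/3) × 1.5 = −1.0 under the week-by-week schedule. That is about a tenth of 9.8, if the scales correspond.

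**The case against.** The case for leaving the design alone is substantial.

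- **Mechanism.** Each condition is one meal, conditions fall in successive weeks, participants fast from the evening before, and the outcome is measured about two hours after eating. Nothing in the protocol suggests that one breakfast alters a score a week later. The learning and memory task is a 90-second digit-symbol coding test, so its name is weak support for lasting learning. This stands and sets the weight of the point.
- **Direction.** A gain carried over from the adequate week shrinks an adequate-versus-comparator contrast. It works against the hypothesis and would not create a false positive. This stands for that example.
- **Wording.** Counter-balanced is a normal description of balance over weeks, so it is incomplete here and not false.
- **Analysis.** A carry-over sensitivity analysis is commonly left to the statistical analysis plan, so its absence here is no fault. The set of orders, however, is fixed in this document and limits what that analysis can do.

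A reader might infer more than the documents support:

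- *That ordinary practice effects bias the breakfast comparisons.* Step 4 shows that they cancel with equal sequences.
- *That carry-over cannot be tested with three orders.* The full model uses all nine sequence-by-week means, so its fit to those means cannot be checked. The carry-over contrasts are still estimable and can be tested against within-participant error. The adjusted analysis is inefficient, not uninformative.
- *That the trial loses power as planned.* Unadjusted variance is 2σ²/N under either design, and the protocol gives no standard deviation or within-person correlation from which to compute power.
- *That participants will foresee their no-breakfast week and change behaviour.* The protocol does not say that they are told the orders. With six orders, week 3 is still determined once week 2 is known.

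The two printed order sets also need reconciling, but that is a separate matter. The Abstract's strings would match the week-by-week schedule if they listed the groups receiving each breakfast in turn, although its wording speaks of assigning participants to sequences. The present point holds on either reading.

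**Conclusion.** The point holds as a design improvement, not as an error. Under either printed schedule, week position is balanced and the preceding breakfast is not. A one-unit carry-over specific to one condition shifts two of the three contrasts by 2/3 unit. Adjusting for it with three orders retains 20% efficiency, against 80% with six.

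These ratios assume equal sequence sizes, first-order carry-over only, and an additive model with constant within-participant variance. They do not depend on the unstated standard deviation. The size of any real differential carry-over is unknown; after a week it is probably small, and the 1.5-point illustration is an assumption. The reason to act is that better protection is available at almost no cost.

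**What to change.** Randomise within city and sex to all six orders: ABC, BCA, CAB (the Abstract's three) and ACB, BAC, CBA (those of the week-by-week schedule). That gives 132/6 = 22 per order per city, of whom 66/6 = 11 are men and 11 women, and 44 per order over both cities. N stays at 264. Each breakfast is still served to 2 × 44 = 88 people each week.

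Revise the Abstract, Participants and study design (with Fig. 1) and Study procedure so that all describe the same six orders and say that both week and preceding breakfast are balanced. Add one sensitivity analysis with week and first-order carry-over terms.

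The cost is a new randomisation list and six orders to track instead of three, with no extra participants, visits or meals. Six orders do not remove differential carry-over from the unadjusted analysis. They halve its size and spread it: carry-over from the adequate week alone would shift both hypothesis contrasts by 1/3 unit, whereas a single cyclic set shifts one of them by 2/3 and leaves the other untouched.

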**Discussion:**

The present study will be the first investigation of the effect of breakfast food type and quality on cognitive function amongst white-collar workers in China. We predict that a nutrition-adequate breakfast, compared with a nutrition-inadequate breakfast and no breakfast, will significantly improve short-term cognitive function. The results of this study should provide scientific evidence of the effect of breakfast quality on cognitive function and provide scientific data to inform nutrition education strategies and promote a healthy lifestyle.

**Trial registration:**

Chinese clinical trial registry (Primary registry in the WHO registry network) Registration number: ChiCTR-IPR-15007114. Date of registration: August 25, 2015.

## Background

As the first meal of the day, breakfast plays an important role in supplying energy and nutrients [1]. After sleeping through the night, the human body needs to refresh and regain energy and nutrients in time to engage in physiological activities. A high-quality breakfast can provide adequate energy and nutrients for working and learning activities [2]. In contrast, a low-quality breakfast leads to lower work efficiency, a large compensatory increase in food intake at the next meal and excessive burden on the gastrointestinal tract [3]. Previous studies have indicated that skipping breakfast no or consuming a low-quality breakfast is harmful for health [4, 5]. An adequate breakfast can not only maintain the body’s needs for activities but also reduce the risk of diabetes, osteoporosis, obesity, cardiovascular and cerebrovascular disease and other chronic diseases [6]. Research findings have demonstrated that people who eat breakfast every day have a 35 to 50% lower risk of obesity and diabetes than their counterparts who do not eat breakfast or eat breakfast occasionally [7].

Another study has revealed that skipping breakfast or eating a low-quality breakfast have a negative effect on cognitive function [8], thus resulting in a decline in brain excitability, the emergence of a slow response and a reduction in attention. In the morning, glycogen stores are significantly depleted after digestion over the course of the night [9]. Glucose is the main fuel for brain function, and optimal cognitive function requires the maintenance of a stable blood glucose level [10]. Breakfast has a direct effect on blood glucose levels and, in turn, blood glucose levels have a direct effect on cognitive function [11, 12]. In general, the brain performs best when the blood glucose level is in the range of 80–120 mg/dL [13]. With the gradual depletion of blood glucose and, consequently, energy consumption, people begin to feel hunger and fatigue and experience a decline in cognitive function [14]. A number of studies have reported that skipping breakfast lowers cognitive function and work efficiency [15–17]. Therefore, breakfast is considered to be the most important meal of the day for nutritional intake as well as work performance.

Along with the advanced socio-economic development in China, the nutritional status of residents has improved. However, owing to the lack of nutritional knowledge and awareness, the importance of breakfast has not been paid sufficient attention. In one study, 19.6% of participants reported rarely eating breakfast [5]. The percentage of students in primary school, junior high school and high school who eat breakfast every day has been reported to be 97.0, 92.4 and 93.4%, respectively; however, the nutritional quality of their breakfast was found to be generally poor [18].

To date, studies on breakfast and its effects on cognitive function have been conducted mainly on primary and secondary school students in China [16, 19]. Few studies on adults have been reported. Thus, to understand the effects of breakfast on the short-term cognitive function of adults, a three-phase crossover study was designed and will be conducted with white-collar workers in two cities in China. The aim of this study is to investigate whether breakfast consumption has an effect on adults’ short-term cognitive function. The effects of three types of breakfast differing in type of quality and energy on short-term cognitive function, blood glucose level, hunger, satiety and mood in adult white-collar workers will be studied.

## Methods/Design

### Study hypothesis

Participants who eat a nutrition-adequate breakfast will have better cognitive performance than those who eat a nutrition-inadequate breakfast or do not eat breakfast.

### Sample size calculation and participants

In a related study, the average cognitive performance value of people who ate a nutrition-adequate breakfast, a nutrition-inadequate breakfast and no breakfast has been found to be 36.6, 25.9 and 26.8, respectively [20]. Using these results as reference values, in this study, power is set at 0.8, SAS programming was used, and the necessary sample size was calculated. According to the SAS procedures described by Hu [21], we calculated the sample size as 117 in one city. If the dropout rate is 10%, a total of 130 participants will be needed. Given that the participants will be divided into three groups, and to achieve equal group sizes, 44 participants will be needed for each group. Therefore, 132 participants will be needed for the three groups to include an equal number of men and women in one city. Because this study will be conducted in two cities, 264 total participants will be recruited.

### Participants and study design

Participants will be recruited from two cities, Shenyang and Chongqing, China. Shenyang is located in northeast China, whereas Chongqing is located in southwest China.

The inclusion criteria will be: white-collar workers aged 25–45 years involved mainly in office work, who engage in brain work and are amenable to skipping breakfast.

The exclusion criteria will be: individuals with mental illness, oral disease or other severe diseases; pregnant women and nursing mothers; individuals who have a tendency to lose weight; and individuals who never eat breakfast.

This crossover study will last for three weeks. Participants will be randomly assigned to one of three groups (Group A, Group B, and Group C). In the first week, Group A will be provided with a nutrition-adequate breakfast, Group B will be provided with a nutrition-inadequate breakfast, and Group C will be provided with no breakfast. Each participant will complete tests of blood glucose level, mood, hunger and satiety, and cognitive function. In the second week, Group A will be provided with no breakfast, Group B will be provided with a nutrition-adequate breakfast, and Group C will be provided with a nutrition-inadequate breakfast. Each participant will complete blood glucose level, mood, hunger and satiety, and cognitive function tests. In the third week, Group A will be provided with a nutrition-inadequate breakfast, Group B will be provided with no breakfast, and Group C will be provided with a nutrition-adequate breakfast. The blood glucose level, mood, hunger and satiety, and cognitive function will be tested again. All participants will take the tests in three successive weeks, and each participant will be tested in three breakfast treatments: nutrition-adequate breakfast, nutrition-inadequate breakfast, or no breakfast. The study design is presented in Fig. 1.

**Fig. 1 Fig1:**
[figure not shown]
The study design

### Screening questionnaires

A screening questionnaire will be used to acquire general information about participants and to exclude participants for medical reasons (including anaemia or other blood disorders, food allergies, diabetes or glucose intolerance, other acute or chronic illnesses/diseases, colour blindness, severe learning disabilities and mood disorders). The screening questionnaire is a combination of self-designed questionnaire items and a standardized questionnaire. The self-designed questionnaire includes items to measure demographic characteristics, including age, gender, marital status, education level, occupation, smoking and drinking habits and frequency of breakfast eating. The standardized questionnaire includes a breakfast nutrition survey and a breakfast and nutrition knowledge survey.

